## Abstract

**Introduction:**

Significant risks to the health of humans and ecosystems are posed by environmental pollution, urban warming, and fragmentation, which are primary urban factors that contribute to the deterioration of urban ecosystems. The purpose of this multidisciplinary study is to compare greenspaces in university campuses and the host cities in order to assess how valuable they are for promoting human and ecosystem health in Nigeria.

**Methods:**

Mixed-methods research that will be conducted in five tertiary institutions and their host cities in southwestern Nigeria. Based on the objectives, the study is divided into four work packages (WP). WP 1 will use suitable sampling traps and scheduled field observations to quantify the diversity of plants and pollinators. Quantitative evaluation of well-being and mental health will be done in WP 2. In WP 3, the relationship between ecosystem health and mental health will be examined and in-depth interviews will be used to explore the socioecological perceptions and interaction of people with specific indicators of ecosystem health in greenspace. In WP 4, a nature-based intervention will be developed and evaluated in a pilot study to determine its feasibility and acceptability.

**Results:**

The 2023 TETFund National Research Fund Intervention provided funding for this work, which is currently ongoing and results are not yet available.

**Conclusion:**

This project will provide scientific knowledge to support evidence-based policy for relevant stakeholders and regulatory organisations, with the goal of promoting greenspace infrastructure in Nigerian tertiary institutions. This article is focused on describing the research design, as the study is currently on-going hence, there is no conclusion yet.

## Introduction

Human well-being is significantly impacted by urbanisation, which also has an effect on the public, mental, and economic health of urban ecosystems. Urbanisation is a growing global problem to human and environmental health due to increased human migration into urban cities [1]. Urbanisation is closely linked to key drivers of global change, many of which are concentrated in metropolitan areas. These drivers include urban warming, environmental pollution, fragmentation, and habitat loss. These factors affect the distribution of biodiversity, human livelihood, and the socioecological relationships that sustain ecosystem health and human well-being in urban landscapes.

Urban greenspaces hold the potential to provide nature-based solutions, as noted by [2], especially in light of the expected growth in urban land cover and population size, particularly in tropical regions [3]. **However,** more research is still needed to determine how greenspaces improve the health of urban residents by fostering a diverse population of ecologically significant species, including pollinators and plants, as well as mitigating the negative consequences of urbanisation.

University campuses are widely acknowledged to provide a chance for a potentially healthy greenspace framework that incorporates advantages for human and environmental health inside the urban matrix. Moreover, they serve as a sentinel landscape for the prompt exploration of the possible advantages of greenspace for human health and biodiversity. This is especially crucial in some developing countries, like Nigeria, where university campus landscapes are better designed to integrate greenspaces than host city landscapes, where greenspaces are primarily on the periphery and are more closely related to rural than urban environments [4].

Studies examining how pollinator health affects human health through their direct and indirect effects on plant diversity and greenspace quality are generally lacking [5]. This is despite the wealth of evidence suggesting pollinator and plant diversity as a limiting factor of ecosystem health and the quality of greenspaces [6–8]. This is an important factor to take into consideration when managing greenspaces since other elements of the environment (for example pests or invasive species) may not be the best indicators of how beneficial greenspace may be for human health.

Therefore, multidisciplinary research is required to determine the relationships between ecosystem health in urban greenspaces and human health using appropriate socioecological context, such as that found in university greenspaces. The aim of this study is to determine the value of urban greenspaces on university campuses versus their host cities in promoting ecosystem and human health. The specific objectives are to assess the diversity of pollinators, plants, pollinator-plant interactions and landscape proportion of green area as indicators of ecosystem health in greenspaces on university campuses and their host cities; evaluate the self-perceived mental health indices of people living close to greenspaces on university campuses and in the host cities; determine the relationship among diversity of pollinators, plants, pollinator-plant interactions, landscape proportion of green area and the self-perceived mental health indices of people living close to greenspaces on university campuses and in the host cities; and develop a nature-based intervention using findings from the first three objectives. This protocol aims to present the research design for this study which is currently in progress.

## Materials and methods

### Study location

Five university campuses and their host cities will be surveyed in southwest Nigeria, within the West African Guinea Biodiversity Hotspot, one of the richest biodiversity hotspots in the world with several endemic species [9] Fig 1. Surveys will be carried out in the following universities and host cities; Obafemi Awolowo University, Ile-Ife; University of Ibadan, Ibadan; Federal University of Technology, Akure; Redeemers University, Ede; Adeyemi Federal University of Education, Ondo. These universities have greenspaces integrated within the academic and administrative areas as well as the staff and student residential areas.

**Fig 1 pone.0317386.g001:**
[figure not shown]
Map of study area.

### Study design

This study is mixed-methods research that is divided into four work packages (WP) based on the outlined objectives.

#### WP 1: Survey of pollinator and plant diversity and landscape proportion of green area as indicators of ecosystem health.

In each of the selected five university campuses and host cities, at least two study sites will be identified per university campus or host city. Study sites will be public greenspaces such as playgrounds, parks and gardens with size ranging from 900 m^2^ to 2500 m^2^. In each sampling location, a site will be defined as a fixed 25 m x 25 m plot where sampling of plants and pollinators and observation of plant-pollinator interactions will be conducted. Fieldwork will be conducted quarterly, to ensure that sampling is conducted in rainy and dry seasons over a one-year period.

During the period of observation, the identity of every insect and flower visited, as well as the number of visits the insect made to the plant within each 25 m x 25 m study site will be noted and recorded. Furthermore, the identity of every plant in each site will be determined, and flower abundance of each plant will be estimated by counting individual flower units. Further, pan traps (bowls of 1 L capacity) of colour white, yellow and blue (a total of twelve bowls per site) will be used to collect diverse insect pollinators in each study site. The bowls will be half-filled with water and few drops of liquid detergent (to break surface tension and enhance insect trapping), and will be deployed in each site for a 24-hour period according to [10]. Insects caught in pan traps will be preserved in 75% ethanol until sorting and identification of insect pollinators. Sampled plants will be identified at the herbarium of Obafemi Awolowo University (OAU) and herbarium collections of other universities while insect pollinators will be identified using identification keys such as [11–13] and with reference collection at the AG Leventis Museum of Natural History Obafemi Awolowo University, Ile-Ife and Museum collections of other universities.

The landscape proportion of green area for each study site will be determined with Landsat images using Geographic Information System (ArcGIS Pro Environmental Systems Research Institute, ESRI, California). This will be computed across a gradient of nearness to each study site at 250 m, 500 m, 1000 m, 2000 m and 4000 m radii around each study site.

Data analysis: Pollinator-plant interaction data will be used to construct plant-pollinator networks using the bipartite R package [14]. Quantitative networks can be interpreted using network metrics derived from the estimates of interaction strength and frequency [15]. Plants, pollinators and landscape variables will be analysed using Generalized Linear Mixed Effect Models and Permutation Analysis of Variance (PERMANOVA). All analysis will be conducted in R.

#### WP 2: Survey of mental health indicators.

This will involve a cross-sectional survey and a comparative study.

**Sample size determination**

The minimum sample size will be determined using the formula for calculating sample size for the comparison of two independent proportions. Based on a WHO Report [16], the prevalence of mental wellbeing in Nigeria was 80% and it is assumed that this study will be able to detect about 15% difference between the prevalence of wellbeing among adults in the university community and adult within the host city. Therefore, the estimated minimum sample size per group will be 256 x 2 = 512. Hence, in the five universities campuses and the respective host cities, we will sample 2560 respondents.

Study population: The respondents will be recruited from the five university campuses and the respective host cities. The respondents that meet the inclusion criteria and give written consent will be randomly recruited until the required number is complete in each study location. We will control for age, sex and level of education between the comparative groups.

Participants will be selected according to the criteria given below

Inclusion criteria will be as follows:

(i) Participants to be recruited will be individuals aged 18 years and above living within the university and those living in the host community.(ii) They must have been living for at least 12 months within the study areas.

Exclusion criteria will be as follows:

(i) Individuals aged less than 18 years, those living less than 12 months within the study areas.(ii) Those who do not give consent

Measures: Data will be collected on respondents sociodemographic details, general health and wellbeing, perception of greenspace, multidimensionality of wellbeing using 23-item version of PERMA wellbeing scale [17] and mental health indicators which include depressive symptoms using the Patient Health Questionnaire (PHQ-9) [18]; anxiety symptoms using the Generalized Anxiety Disorder 7-item (GAD-7) [19]; perceived stress using Short Form Perceived Stress Scale (PSS-4) [20]. In addition, suicidal ideation and social connectedness will be measured using Suicidal Ideation Attributes Scale (SIDAS) [21] and Social Connectedness Questionnaire-Revised [22] respectively.

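### The WP2 sample size allows for no variation between locations, so the detectable difference of about 15% depends on an unstated ICC; the figures 256 and 512 also need restating

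*Protocol article*

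**What the plan says.** The Protocol article, WP 2, Sample size determination, names its method: "The minimum sample size will be determined using the formula for calculating sample size for the comparison of two independent proportions". The inputs are a reference figure, "the prevalence of mental wellbeing in Nigeria was 80" per cent, and an effect: "it is assumed that this study will be able to detect about 15% difference between the prevalence of wellbeing" in the university community and in the host city. The result is "Therefore, the estimated minimum sample size per group will be 256 x 2 = 512". The total follows: "in the five universities campuses and the respective host cities, we will sample 2560 respondents".

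On recruitment, the same section says "The respondents will be recruited from the five university campuses and the respective host cities", with respondents "randomly recruited until the required number is complete in each study location". Age, sex and level of education are to be controlled for between the groups. The section gives no ICC, design effect, alpha, power, non-response allowance or direction of the 15%. It does not say whether the 15% is absolute or relative, and it names no WP2 analysis model.

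**The concern.** The formula treats each respondent as an independent unit of evidence on campus versus city. Here the setting is fixed by where a person lives, and everyone in one location shares that location. The overall comparison therefore has five units against five, with respondents nested inside them. If wellbeing varies between places for reasons other than setting, that variation adds to the error of the comparison, and more respondents per place do not reduce it. The study's own objectives relate differences between places to mental health, so zero variation between locations cannot simply be assumed.

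At stake is whether the stated detectable difference can be relied on. If the analysis followed the sizing assumption, the validity of the p-values would be at stake too. WP2 results feed the quantitative part of WP3 and the choice of intervention in WP4, so an error here would carry forward.

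Two smaller faults sit in the same lines: the label on 512, and a figure of 256 that the stated inputs do not yield at usual settings.

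**Working it through.** **1. The plan's totals.** 256 × 2 = 512 and 512 × 5 = 2,560, so the multiplication is right. An even split gives 2,560 / 10 = 256 per location and 5 × 256 = 1,280 per setting. Hence 512 is the total of two groups in one pair, not the size of one group.

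**2. Does 256 follow from the inputs?** Standard formula, p̄ = (p1 + p2)/2:

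n per group = [z(α/2)·√(2p̄(1−p̄)) + z(β)·√(p1(1−p1) + p2(1−p2))]² / (p1−p2)²

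For 80% versus 65%, two-sided 5%, 80% power: [1.96 × 0.6315 + 0.8416 × 0.6225]² / 0.0225 = 137.9, so 138. The other readings, at two-sided 5%:

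| Contrast | 80% power | 90% power |
|---|---|---|
| 80 vs 65 | 138 | 185 |
| 80 vs 95 | 76 | 101 |
| 80 vs 68 (15% relative, downward) | 209 | 279 |
| 80 vs 92 (15% relative, upward) | 131 | 174 |

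None is 256. Figures near 256 need settings that the article does not state. Examples are 80 vs 65 at 95% power with 10% non-response (about 254), 80 vs 68 at 80% power with 20% non-response (251 to 262), or 80 vs 65 at 1% alpha and 90% power with the unpooled variance (256.3).

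**3. Allowing for location.** The ICC is an assumption, with range 0.01 to 0.05. With m = 256 per location:

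- design effect DE = 1 + 255 × ICC
- effective n per setting = 1,280 / DE
- SE = √[(p1(1−p1) + p2(1−p2)) / effective n]
- power from the noncentral t with noncentrality |p1−p2| / SE, on 8 df (ten locations, unpaired) or 4 df (five pairs, no reduction in variance credited)

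Example, 80 vs 65 at ICC 0.02: DE = 6.10; effective n = 210; SE = √(0.3875 / 210) = 0.043; noncentrality = 0.15 / 0.043 = 3.49. Against critical values of 2.306 (8 df) and 2.776 (4 df), power is 86% and 74%.

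| ICC | DE | Effective n per setting | Power 80 vs 65 (8 df / 4 df) | Detectable drop from 80%, 80% power, 8 df |
|---|---|---|---|---|
| 0.01 | 3.55 | 361 | 98% / 92% | 10 points |
| 0.02 | 6.10 | 210 | 86% / 74% | 14 points |
| 0.05 | 13.75 | 93 | 53% / 43% | 21 points |

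Power for 80 vs 65 falls below 80% above an ICC of about 0.025 (8 df) or 0.017 (4 df). If the 15% is relative (80 vs 68), those limits are about 0.015 and 0.010.

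**4. The other direction.** For 80 vs 95 the variance sum is 0.16 + 0.0475 = 0.2075 instead of 0.3875. Power is 99% / 94% at ICC 0.02 and 79% / 67% at ICC 0.05.

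**5. If clustering were ignored.** A pooled test on 1,280 versus 1,280 as independent respondents has true type I error 2·[1 − Φ(1.96/√DE)], which is about 30% / 43% / 60% at ICC 0.01 / 0.02 / 0.05.

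**The case against.** The strongest defence is that the calculation is made once and repeated in each of five pairs. Read per pair, it compares prevalence in two named communities. For that descriptive question independent proportions is a fair formula, and 256 versus 256 has 97% power for 80 vs 65 under simple random sampling. Read as pooled, the total is five times the calculated minimum, which absorbs a design effect of 5, or an ICC of (5 − 1)/255 ≈ 0.016. Both points stand. The per-pair reading, however, cannot separate the campus setting from anything else that differs between those two places, and the study's aim concerns campuses versus host cities in general.

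The paired figures above are also a worst case, because they pay for pairing in degrees of freedom and credit no gain. With an assumed within-pair correlation of 0.5, power for 80 vs 65 is 92% at ICC 0.02 and 67% at 0.05. Control for age, sex and education may also reduce variation between locations.

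A reader might infer that this design cannot detect a 15% difference. The documents do not support that. They give no ICC, and power is adequate over part of the plausible range, more so for 80 vs 95. A reader might also infer that the WP2 results will carry a type I error of 30% to 60%. That would need an unadjusted pooled test. The article names no WP2 model, and an analysis plan not shown may handle location properly.

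Alpha, power and non-response are details that an article may condense, so their absence alone is no fault. Here they matter because the figure printed does not follow from the inputs printed beside it.

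**Conclusion.** The point holds in a conditional form. The sizing formula does not match an exposure fixed at location level with five locations per setting, and it allows for no variation between them. The detectable difference of about 15% in the overall comparison is therefore assured only at a low ICC: below about 0.025 (8 df) or 0.017 (4 df, no pairing gain) for 80 vs 65, lower if the 15% is relative, and higher for 80 vs 95 or if pairing removes shared variance. These limits rest on 256 respondents in every location, two-sided 5%, a target of 80% power, and an ICC that has to be assumed.

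Two statements are wrong or unsupported without any assumption about ICC. The figure 512 is not a per-group size, and the stated inputs do not give 256 at two-sided 5% with 80% or 90% power under any reading of the 15% tried here. The mislabel changes no total. For 80 vs 65, 256 is more than the formula requires.

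**What to change.** - Keep 2,560 respondents. Describe them as 256 per location, 512 per campus–city pair and 1,280 per setting.
- State what lies behind 256: alpha and sidedness, power, direction of the 15%, whether it is absolute or relative, and any non-response allowance.
- Replace the single detectable difference with values over a stated range of ICC, for example 0.01 to 0.05.
- Make the pooled comparison across the five pairs primary, with location as a random effect and pair in the model, or as a paired location-level analysis. Use small-sample degrees of freedom in either case.
- Report single-pair differences as descriptive of those two places.

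The cost is wording and analysis code, with no extra respondents. The downside is a less favourable stated detectable difference and wider confidence intervals.

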## Limitations

The anticipated limitation of this study is the likely variation in demographics of study participants in the universities compared to the host cities. We plan to address these limitations by ensuring wide spectrum of study participants ranging from students, middle-class workers and non-literate workers living both in the universities and the host cities are recruited during the study.

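### WP 2 names age, sex and education as its controls but not student or occupational status, so the campus–city comparison is likely to keep residual confounding

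*Protocol article*

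**What the plan says.** All references are to the Protocol article.

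- **Eligibility (WP 2).** The population is "individuals aged 18 years and above living within the university and those living in the host community", with at least 12 months' residence. Student status and occupation play no part in eligibility.
- **Recruitment (WP 2, Study population).** Eligible people who consent "will be randomly recruited until the required number is complete in each study location". No strata, quotas, matching or weights are described.
- **Control of confounding (WP 2, Study population).** "We will control for age, sex and level of education between the comparative groups". The method of control is not stated.
- **Data collected (WP 2, Measures).** "Data will be collected on respondents sociodemographic details, general health and wellbeing, perception of greenspace", among other items. The sociodemographic items are not listed.
- **Limitations.** "The anticipated limitation of this study is the likely variation in demographics of study participants in the universities compared to the host cities". The response to this is "ensuring wide spectrum of study participants ranging from students, middle-class workers and non-literate workers living both in the universities and the host cities are recruited".

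No section adds student or occupational status to the controlled variables.

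**The concern.** Living on campus and being a student are tied together by the setting: the Study location section says these universities include staff and student residential areas. Student status is also plausibly related to what WP 2 measures, namely wellbeing, depressive and anxiety symptoms and perceived stress. A variable related to both the exposure group and the outcome confounds the comparison unless it is balanced or adjusted for.

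The plan offers two measures. One controls three variables, none of which is student status or occupation. The other ensures that each participant group is present in both settings. A campus sample made up mostly of students and a city sample made up mostly of workers would satisfy the second measure and still differ in mix.

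The campus–city contrast in mental health is at stake, and so is what follows from it. WP 2 data enter the WP 3 models, and WP 1–3 results are used to choose the indicators on which the WP 4 intervention is built.

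**Working it through.** **1. The plan's own figures.** The article gives 256 per group: 256 × 2 = 512 per campus–city pair, and 512 × 5 = 2560 in total, so 1280 per setting. The multiplication is consistent. The 256 cannot be confirmed, because alpha, power and non-response are not stated. The present point does not depend on it.

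**2. What the three controls capture.**

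| Group named in Limitations | Captured by age, sex, education? |
|---|---|
| Non-literate workers | Largely, through education |
| Students | Partly, through age and education |
| Middle-class workers | Partly; not separated from students of the same age and schooling |

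What remains is mainly the contrast between a student and a worker of similar age and schooling.

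**3. Size before any adjustment.** Let s₁ and s₀ be the student shares on campus and in the city, and g the gap in wellbeing prevalence between students and others. With no true campus effect, the difference seen is

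bias = (s₁ − s₀) × g.

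The article gives neither the shares nor the gap. Assumed here: s₁ = 60–80%, s₀ = 20–30%, g = 10–15 points.

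| s₁ | s₀ | g = 10 points | g = 15 points |
|---|---|---|---|
| 0.60 | 0.30 | 0.30 × 10 = 3.0 | 0.30 × 15 = 4.5 |
| 0.60 | 0.20 | 0.40 × 10 = 4.0 | 0.40 × 15 = 6.0 |
| 0.80 | 0.30 | 0.50 × 10 = 5.0 | 0.50 × 15 = 7.5 |
| 0.80 | 0.20 | 0.60 × 10 = 6.0 | 0.60 × 15 = 9.0 |

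The range is 3 to 9 points. Against the target of about 15 (read as percentage points), that is 3/15 = 20% to 9/15 = 60%. Wider assumptions (share difference 20 to 80 points, gap 5 to 15 points) give 0.20 × 5 = 1 to 0.80 × 15 = 12 points. Equal shares give zero. The sign depends on whether students fare better or worse than others, so the bias could mimic a campus effect or hide one.

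**4. Why a few points matter at this sample size.** With 1280 per setting, a prevalence of 80% and clustering ignored,

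SE = √(2 × 0.80 × 0.20 / 1280) = √0.00025 = 0.0158, or about 1.6 points.

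An unadjusted bias of 3 points alone would reach two-sided p < 0.05 about 47% of the time, and one of 9 points almost always.

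**5. Size after adjustment for age, sex and education.** This would need the joint distribution of these variables with student status. The article gives none of it, so the figures in steps 3 and 4 describe the bias before adjustment and do not estimate what remains.

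**The case against.** The strongest reply is that the sentence on controls does not say it is exhaustive. It stands under Study population, WP 2 has no analysis paragraph in the article, and a fuller protocol or analysis plan could list more covariates. That stands: a reader might infer a fixed, closed adjustment set, and the document does not support this. It remains true that the article names three variables for this comparison and stops there, although it describes its participants elsewhere by student and worker group.

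A reader might also infer that the authors predict an imbalance in occupational mix. They do not. The expected imbalance is in demographics generally, and the groups appear only in the remedy. Age, sex and education are themselves demographics, so part of what is anticipated is already covered. This narrows the point to residual confounding.

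Recruiting every group in both settings is also useful, because adjustment needs that overlap. It does not replace adjustment.

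Finally, it would go too far to say that a student–worker difference will be reported as a greenspace effect. The objectives separate describing mental health in the two settings from relating it to ecosystem indicators, and the models for the latter are left open.

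**Conclusion.** The point holds as one of likely residual confounding. The named controls capture student and occupational status only in part, and presence of all groups in both settings does not balance their proportions. The amount left after adjustment for age, sex and education cannot be computed from the article. The only available figure is the bias of 3 to 9 points before adjustment, and it rests wholly on assumed student shares and an assumed wellbeing gap. The bias would be nil if the shares were equal or if student status were unrelated to wellbeing. The change is worth making because it is cheap and the sample is large enough for a bias of a few points to look like a finding.

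**What to change.** Add student/occupational group to the variables named for control, both in the WP 2 campus–city comparison and in the WP 3 models that use the WP 2 data. Report the campus–city difference within each group as a sensitivity check. Confirm that the sociodemographic section of the questionnaire records student status and occupation, since the article does not list its items. Let the Limitations section refer to this adjustment alongside the recruitment of all groups.

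The cost is one covariate, slightly wider intervals, and sparse cells where a group is rare in one setting (non-literate workers living on campus, for example). Within-group results there should be read with caution.

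Equal quotas per group are not recommended. They would replace the stated random recruitment, and the sample would need reweighting before it could describe prevalence in each setting. The groups named in Limitations also may not cover all adults, such as retired or unemployed residents, so the covariate needs a category for the others.
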